### 2.6. Data Sources/Measurement

We train all data collectors in accurately obtaining the variables of interest. We use paper source data and electronic case report forms to document all study variables of interest.

#### 2.6.1. Dermatological Examination

The investigator performs the dermatological examination during the visits together with a subject's interview on medical history and treatments to check the subject's eligibility.

#### 2.6.2. Measurements of Skin Physiology

We measure the physiological skin parameters of the females and the newborns at one area of the right inner forearm. All measurement procedures are based on internal standardized operating procedures as part of the quality management system of the study site. Before the assessment measurements, subjects rest for 30 minutes in a room with controlled environmental conditions (22°C ± 2°C room temperature; 50% ± 10% relative humidity) for acclimatization. During acclimatization, the skin of the investigational sites is uncovered and exposed to ambient air. The parameters are measured in the following order: skin swab, TEWL, SCH, pH, Cutometry, OCT, and Visioscan. The order and exact skin areas are arranged in such a way that any measurement procedure will not affect the readings of the subsequent measurement [25].

#### 2.6.3. Skin Surface Topography

Based on the definition of the EEMCO guidance [26], the skin surface topography is measured with “Visioscan VC 98 USB” (Courage + Khazaka Electronics GmbH, Germany). The skin is scanned with a high-resolution camera to measure mean roughness. Mean roughness (Rz) is presented in means (SD) and median (IQR).

#### 2.6.4. Epidermal Thickness

Optical coherence tomography (OCT; THORLABS TELESTO, Spectral Domain OCT System) allows for a noninvasive imaging of the epidermis [27, 28]. Based on the obtained images, epidermal thickness is calculated using internal standardized operational procedures.

#### 2.6.5. Skin Stiffness and Elasticity

The total extensibility of the skin (Uf, mm) is measured using the “Cutometer MPA 580” (Courage + Khazaka Electronics GmbH, Germany) according to guidance by the EECMO group for the assessment of biomechanical skin properties [29].

#### 2.6.6. Transepidermal Water Loss

TEWL (*g* per hour per m^2^) is measured using the “Tewameter TM 300” (Courage + Khazaka, Electronics GmbH, Germany). This is an open chamber method, and the results are compared to published reference values in adults and newborns [10, 30]. Empirical evidence supports the reliability of this estimate at the volar forearm [31].

#### 2.6.7. Skin Surface pH

Skin pH is measured using the “Skin-ph-Meter®PH 905 device” (Courage + Khazaka, Electronics GmbH, Germany). This investigation is highly reliable at the volar forearm [31] when applying the standard operating procedures. Reference values of human skin have been reported to range from 4 to 6 [32, 33].

#### 2.6.8. Stratum Corneum Hydration

SCH is measured by using the “Corneometer CM 825” (Courage + Khazaka, Electronics GmbH, Germany). The measurement is based on the differences in the dielectric constant of water and other substances within the stratum corneum. The arbitrary units for SCH measurements range from 0 to 120, with higher readings indicating higher SCH [34].

#### 2.6.9. Skin Microbiome and Analysis

We follow the analytic test methods put forward by McInnes and Cutting in the “Human microbiome project,” for describing the microbiome distribution of bacterial species in this study [35]. According to the latest recommendations by the involved test laboratory, a swab is taken with aseptic techniques at the volar forearm. The swab is moistened with sterile NaCl 0.9% + 0.5% Tween 20 solution and then rubbed back and forth for 30 seconds. Afterwards, the swab head is inserted into the tube containing DNA/RNA Shield of Zymo Research, Irvine, USA. The head of the swab is then aseptically cut from the handle, and the tube cap is screwed back in place. The skin microbiome is defined as bacterial diversity. The relative abundance of phylotypes (operational taxonomic units, OTUs) is measured by the alpha diversity and Shannon index.

#### 2.6.10. Hair Measurements

Hair measurements are taken on the central and occipital head area in women and on the central head area in newborns/infants. Standardized macro photographs are taken to measure hair growth and structure. We use the Visiomed D200 evo camera of Vectra H1 Hair Metrix, Canfield Scientific, Fairfield, USA. The camera is placed on the selected area of the participant's scalp to take a picture as a noninvasive method. At the selected area (central and occipital), the hair is parted with a comb, preparing the hair region for investigation. The following quantitative hair measurements are calculated automatically by the software system: hair count per cm^2^, sum of hair width per cm^2^, terminal to vellus ratio, and average hair width (*μ*m). Additionally, the hair colour is estimated by a 10-point hair colour scale [36].

### 2.7. Bias

#### 2.7.1. Information Bias

During the study period, the risk of losing participants is addressed with proper information and close support in the beginning and throughout the study. An expense allowance is provided. If a woman is included during the early phase of pregnancy, a phone call is scheduled three months after inclusion or at the latest one week before the due date. This phone call allows us to check the current situation, as well as to check the date for the second visit (t1). Similar to this procedure, the women are called one week before the scheduled third visit (t2). If the women are not reachable, phone calls are repeated twice, and in addition, emails are sent and repeated twice. If there is no response, a letter by registered post is sent. If there is no response after all contact attempts, the woman is then excluded from the study.

In order to estimate the outcomes accurately, all investigations are following internal standardized operating or technical procedures, with staff exclusively allocated to the study performing them.

#### 2.7.2. Selection Bias

Due to the sampling of eligible women restricted to one geographical area, a potential sampling bias is addressed by comparing all relevant characteristics of the included women with national data. Due to the voluntary nature of inclusion in the study, a sampling bias might occur. Therefore, relevant characteristics of the included women are compared to the study population to evaluate potential differences. To address a potential response bias, the age distribution and the number of pregnancies of the included women are considered and compared to national data of the mean age of women at delivery of their first child.

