### 2.4. Participants

Participants are pregnant females between 18 and 45 years old and residing in Berlin (Germany). Prerequisites for study inclusion are individual written informed consent, clinically healthy skin and hair appearance, as well as being free of any dermatological condition. Skin afflictions, which may interfere with the study assessments, especially atopic dermatitis, scars, or other lesions at the investigational site result in exclusion. Women must be of general good and stable health as confirmed by medical history and by a physical examination. They must accept to abstain from sunbathing and solariums and to agree to stay consistent in using their individual skin cleaning and caring routines during the study.

Women are excluded due to regular smoking, regular alcohol intake, or criteria related to diseases such as any dermatological condition or skin affliction, which may interfere with the study assessments. These could be any inflammatory dermatosis (psoriasis, atopic dermatitis, or other lesions at the investigational sites) or clinically significant, possibly unstable medical conditions due to pregnancy such as gestosis, eclampsia, or thrombosis. Criteria related to treatments and products such as current topical or systemic treatment possibly affecting the skin (diuretics, cholesterol-lowering drugs, and hormones) during the past four weeks are further exclusion criteria. Additionally, therapeutic ultraviolet radiation or increased ultraviolet exposure within six weeks before inclusion leads to exclusion. For safety, other medical reasons, and any individual reasons, study participation can be stopped.

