### 2.8. Study Size

Due to the exploratory character of this study, formal sample size calculation is not performed. We aim to include 100 pregnant females and their newborns/infants to obtain means and proportions with an acceptable range of uncertainty. A loss-to-follow-up of one-third is assumed resulting in a total of *n* = 150 mothers to be included.

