## Figures and Tables

**Table 1 tab1:** Timeline for women and newborns.

	Inclusion baseline visit during pregnancy (16^th^–36^th^ week) t0	Delivery + 4 weeks t1	Delivery + 6 months (end of the study) t2

Informed consent	*x*	*x* newborn	
Inclusion/exclusion criteria	*x*	*x* newborn	
Medical examination	*x*	*x* ^1^	*x* ^1^
Dermatological examination	*x*	*x* ^1^	*x* ^1^
Skin measurements	*x*	*x* ^1^	*x* ^1^
Skin microbiome	*x*	*x* ^1^	*x* ^1^
Hair metrix analysis	*x*	*x* ^1^	*x* ^1^

*x*
^1^ = visit for mother and baby.

**Table 2 tab2:** Variables.

Variables	Statistics/level of scales	Possible range of measurements	Time of measurement Women	Time of measurement Newborn/infant	Source of information
Age	Metric variable	In years, women In days/months, newborn/infant 18–45 years, women 0–28 d, newborn 1–6 months, infant	Baseline, t0	Delivery + 28 d, t1 Delivery + 6 months, t2	ID card, woman “U-heft,” newborn/infant U3: 4^th^–5^th^ week U5: 6^th^–7^th^ month
Weight	Metric variable	In kg, woman In kg, newborn/infant	Baseline, t0 Delivery + 28 d, t1 Delivery + 6 months, t2	Delivery + 28 d, t1 Delivery + 6 months, t2	Measurement “U-heft,” newborn/infant U3: 4^th^–5^th^ week U5: 6^th^–7^th^ month
Height	Metric variable	In cm, woman In cm, newborn/infant	Baseline, t0	Delivery + 28 d, t1 Delivery + 6 months, t2	Self-reporting, woman “U-heft,” newborn/infant U3: 4^th^–5^th^week U5: 6^th^–7^th^month
Sex	Nominal variable	Female Male		Delivery + 28 d, t1	“U-heft,” newborn/infant
					U1 delivery
Habitation	Nominal variable	Urban Rural	Baseline, t0 Delivery + 28 d, t1 Delivery + 6 months, t2	Delivery + 28 d, t1 Delivery + 6 months, t2	Self-reporting, woman
Newborn/infant's environment	Nominal variable	Apartment House		Delivery + 28 d, t1 Delivery + 6 months, t2	Self-reporting, woman
Course of delivery	Nominal variable	Vaginal birth Caesarean	Delivery + 28 d, t1		“U-heft,” newborn/infant U1 delivery
Vaginal seeding	Nominal variable	Yes No		Delivery + 28 d, t1	Self-reporting, woman
Newborn/infant nutrition	Nominal variable	Breastfeeding Cow-milk-based infant formula (including hypoallergenic (HA) based formula) feeding or combination		Delivery + 28 d, t1 Delivery + 6 months, t2	Self-reporting, woman
Period of newborn/infant nutrition (supplementary feeding)	Metric variable	From week *x* to week x		Delivery + 28 d, t1 Delivery + 6 months, t2	Self-reporting, woman
Gestational age at birth	Metric variable	In weeks		Delivery + 28 d, t1	“U-heft,” newborn/infant U1 delivery

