Dermatological skin assessment, mother	Nominal variable	Coded by ICD11	Baseline, t0 Delivery + 28 d, t1 Delivery + 6 months, t2		Study MD
Dermatological skin assessment, newborn/infant	(i) Eczema (ii) Dry skin (iii) Itchy skin (iv) Rash (v) Flexural dermatitis and/or visible dermatitis (vi) Diaper dermatitis (vii) Hand, mouth, and foot disease	EASI score: (i) Erythema (ii) Edema/papulation (iii) Excoriation (iv) Lichenification EASI score: (i) Severity of signs (1) 0–3 (2) None severe Dry skin: (ii) Desquamation fissures/rhagades (iii) Erythema (iv) Pruritus Itchy skin: (i) If yes: continuous/intermittent Rash: yes/no Diaper dermatitis: yes/no Hand, mouth, and foot disease: yes/no		Delivery + 28 d, t1 Delivery + 6 months, t2	Study MD
Skin care, mother	Open-ended question		Baseline, t0 Delivery + 28 d, t1 Delivery + 6 months, t2		Self-reporting, woman
Skin care, newborn/infant	Open-ended question			Delivery + 28 d, t1 Delivery + 6 months, t2	Self-reporting, woman
Care givers at home	Nominal variable	(i) Father (ii) Sibling (iii) Grandparents (iv) Au pair (v) Nursery nurse (vi) Other		Delivery + 28 d, t1 Delivery + 6 months, t2	Self-reporting, woman
Furred pets at home	Nominal variable	(i) Cat (ii) Dog (iii) Others	Baseline, t0 Delivery + 28 d, t1 Delivery + 6 months, t2		Self-reporting, woman
The atopic predisposition of the mother (at least one parent or sibling with physician-diagnosed AD, asthma, or allergic rhinitis/rhinoconjunctivitis as reported by at least one parent but in otherwise good overall health)	Nominal variable	Yes/no	Baseline, t0		Self-reporting, woman
Antibiotic intake	Nominal variable	Yes/no	Baseline, t0 Delivery + 28 d, t1 Delivery + 6 months, t2		Self-reporting, woman
Alcohol consumption	Nominal variable	Yes/no	Baseline, t0 Delivery + 28 d, t1 Delivery + 6 months, t2		Self-reporting, woman
Skin surface topography roughness: (i) RA (arithmetic mean roughness) in *μ*m (ii) RZ (arithmetic mean roughness from five sampling length) in *μ*m	Metric scaled variable Mean (SD) Median (IQR)	RA: 0.0–100.0 *μ*m RZ: 0.0–100.0 *μ*m	Baseline, t0 Delivery + 28 d, t1 Delivery + 6 months, t2	Delivery + 28 d, t1 Delivery + 6 months, t2	Standardized images via visioscan VC 98 USB (i) RA (arithmetic mean roughness) in *μ*m (ii) RZ (arithmetic mean roughness from five sampling length) in *μ*m Skin area: inner forearm

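### The response-bias check sets women of any parity against the national mean age at first birth, so even a representative sample is expected to differ from the benchmark

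*Protocol article*

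**What the plan says.** Section 2.7.2 (Selection Bias) describes three comparisons. The first sets all relevant characteristics of the women against national data, without naming the figures to be used. The second deals with voluntary participation: "relevant characteristics of the included women are compared to the study population to evaluate potential differences". The third is the subject here. It opens with "To address a potential response bias", states that "the age distribution and the number of pregnancies of the included women are considered", and ends by saying that these are "compared to national data of the mean age of women at delivery of their first child". It is the only one of the three that names a specific benchmark.

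Eligibility in section 2.4 rests on pregnancy, age 18 to 45 years, residence in Berlin and health criteria. Nothing limits the cohort to first pregnancies or first births. Table 2 lists a sibling among the possible caregivers at home, so families with older children are foreseen.

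**The concern.** The two sides of the comparison describe different populations. The sample contains women expecting a first, second or later child; the benchmark is an average over first births only. A representativeness check should have an expected difference of zero when the sample is representative. This one does not, unless later-birth mothers happen to be no older than first-time mothers.

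The sentence also gives the number of pregnancies an age as its comparator. A count cannot be compared with a mean age, so that half of the check has no usable benchmark as written.

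At stake is how the age composition of the cohort is interpreted. Age matters in this study: section 2.9.1 forms subgroups from the outer age quartiles, and section 2.9.2 names age as a main predictor variable. A check with a built-in offset can mislead in two directions. It may report a departure from the national figure that reflects parity alone, or it may show agreement because over-recruitment of younger women has cancelled the offset.

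**Working it through.** **The plan's own figure.** Section 2.8 states: "A loss-to-follow-up of one-third is assumed resulting in a total of *n* = 150 mothers to be included". With a target of 100 and one-third lost, 100 / (1 − 1/3) = 150. This reproduces, and 150 is used below as the number of included women, with 100 as the alternative.

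**Inputs from the article.** n = 150 included or 100 remaining (section 2.8); baseline visit in weeks 16 to 36 (Table 1).

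**Inputs not in the article, therefore assumed.** Share of women not having their first child, q = 0.3 to 0.6; mean age at later births minus mean age at first birth, g = 2 to 4 years; SD of age, 5 years; term at 40 weeks.

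**Expected offset in a representative sample.** Offset = q × g − L, where L is the time from the age record to delivery.

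- L = 0 if age at delivery is used.
- If age at the baseline visit is used, L runs from (40 − 36) × 7 / 365.25 = 0.08 years to (40 − 16) × 7 / 365.25 = 0.46 years.

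**Sampling error.** SE = 5/√150 = 0.408, so the 95% half-width is 1.96 × 0.408 = 0.80 years. For n = 100, SE = 0.5 and the half-width is 0.98 years.

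**Chance that a 95% confidence interval for mean age excludes the benchmark although the sample is representative.** P = Φ(offset/SE − 1.96) + Φ(−offset/SE − 1.96). With n = 150:

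| q, g | L = 0 | L = 0.08 | L = 0.46 |
|---|---|---|---|
| 0.3, 2 years | 0.60 years, 31% | 0.52 years, 25% | 0.14 years, 6% |
| 0.5, 3 years | 1.50 years, 96% | 1.42 years, 94% | 1.04 years, 72% |
| 0.6, 4 years | 2.40 years, about 100% | 2.32 years, about 100% | 1.94 years, about 100% |

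For n = 100 and L = 0 the three rows give 22%, 85% and about 100%.

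**Like-for-like check.** With matched populations and age at delivery, the expected offset is 0 and P is 5%.

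**Masking.** In the middle case with L = 0, a cohort whose mean age is 1.5 years below that of the population it should represent would agree exactly with the first-birth benchmark.

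Over these ranges the offset stays positive. Its size relative to sampling error runs from negligible to decisive.

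**The case against.** The strongest reply is that section 2.7.2 sets no test, threshold or decision rule, and section 2.9 calls all P-values and confidence intervals descriptive. The interval calculation above is therefore a yardstick added here. This stands. A reader might infer that the check will signal a difference in any representative sample; the article does not support that. Parity share, age gap and SD are all assumed, and age taken before delivery works against the offset. For example, q = 0.4 and g = 2 give 0.8 years and z = 0.8/0.408 = 1.96 with age at delivery, but 0.34 to 0.72 years and z of about 0.8 to 1.8 with age at baseline.

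A second reply is that pregnancies may be considered precisely so that first-time mothers can be picked out for the comparison. That is plausible, but the sentence states no such restriction.

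Three further inferences are tempting and do not hold as errors:

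- *Number of pregnancies will not be collected because Table 2 omits it.* Section 2.7.2 itself plans to use it, the medical-history interview in section 2.6.1 could supply it, and the article condenses a fuller protocol.
- *Age at delivery cannot be obtained because age is recorded at baseline.* Maternal age comes from the ID card and the follow-up visits are dated from delivery, so it can probably be derived.
- *The voluntary-participation check compares the women with themselves.* The study population there can be read as the source population.

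Nor does generalisability rest on this check alone: it is one of three descriptive comparisons and feeds no outcome analysis.

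**Conclusion.** The named benchmark does not match the women it is applied to, and a count of pregnancies has no meaningful comparison with it. On the condition that later-birth mothers are older on average, a representative cohort is expected to look older than the benchmark by about 0.6 to 2.4 years before any baseline lag, for the assumed multiparous share of 30 to 60% and gap of 2 to 4 years. With age taken at the earliest baseline visit, the lowest case falls to 0.14 years. An expected offset is shown; a detectable one is not, because the article gives none of the inputs that decide it. The point is minor: a stated comparison needs a different benchmark, and the consequence is confined to describing how representative the cohort is.

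**What to change.** Replace the single benchmark in section 2.7.2 with three matched comparisons:

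1. Age at delivery of first-time mothers with the national age at first birth.
2. Age at delivery of all included women with the national age at all births.
3. Number of pregnancies, or of births, with the national distribution of that same quantity.

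Number of previous births is the item that identifies first-time mothers, since an earlier pregnancy need not have ended in a birth. If it is not already recorded, one self-report question supplies it, and women already enrolled can be asked at a follow-up visit. The other cost is a change of benchmark table, assuming that the national figures can be had by birth order. No outcome, model or sample size changes.

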### 2.8. Study Size

Due to the exploratory character of this study, formal sample size calculation is not performed. We aim to include 100 pregnant females and their newborns/infants to obtain means and proportions with an acceptable range of uncertainty. A loss-to-follow-up of one-third is assumed resulting in a total of *n* = 150 mothers to be included.

### 2.9. Statistical Methods

We will describe the demographic characteristics of the subjects, using absolute and relative frequencies, means, and standard deviations (SD). Metric outcomes will be described using means, SD, medians, and interquartile ranges (IQR) per group and time point. Ordinally, scaled outcomes will be described using medians and IQR per group and time point. Associations of skin parameters between mothers and their newborns/infants will be described using correlation coefficients (Kendall's Tau). Linear mixed models (metric analysis), as well as nonparametric rank-based methods for longitudinal data (ordinal data or skewed endpoints), will be used to assess differences between groups over time (and possible interactions). Furthermore, the Munzel test r (nonparametric) or paired *t* tests (metric observations) will be used to compare paired data. Confidence intervals (95%) will be computed for the effects of interest. Due to the explanatory character of the study, all statistical analyses are exploratory, and thus, all *P*-values and confidence intervals are considered descriptive. If missing values occur, we discuss them on an individual level and use all available cases in the analysis. All statistical methods will be performed using validated software.

#### 2.9.1. Methods to Examine Subgroups and Interactions

The following subgroup analyses are planned: according to age groups of the females, comparisons will be made for Q1/Q4-age-related groups. Due to the predisposition for atopic dermatitis (AD), an analysis for existing or non-existing AD will be made. Because of a possible association between mode of delivery and the skin microbiome, comparisons will be made for vaginal and cesarean delivery.

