#### 2.9.2. Missing Data Management

Because of the long individual follow-up, the attrition rates are difficult to predict. After the inclusion of *n* = 150 women, we assume the number of dropouts to be *n* = 50. Because this is a single cohort of women and their newborns, missing data will not be dependent on different exposures. However, we will compare the groups of subjects with missing data and groups of subjects with complete data regarding main outcome variables to estimate potential bias. Secondly, we will estimate the influence of main predictor variables, such as age, on the occurrence of missing data. Based on the proportion of missing values and the assumed bias, appropriate multiple imputation methods for categorical and continuous variables will be applied [37].

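### The maternal-age subgroup analysis compares only the lowest and highest age quartiles, which loses some precision and hides the shape of the relation; continuous age on all women would do better

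*Protocol article*

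**What the plan says.** Section 2.9.1 lists three subgroup analyses: age, atopic dermatitis and mode of delivery. For age it states that "according to age groups of the females, comparisons will be made for Q1/Q4-age-related groups". It gives the second and third quartiles no role in that comparison.

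Table 2 lists age as a metric variable in years, with the range "18–45 years, women".

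Section 2.9 plans linear mixed models for metric outcomes and rank-based longitudinal methods for ordinal or skewed ones, both to assess group differences over time. It plans Kendall's Tau for associations between mothers and infants. It adds that "Confidence intervals (95%) will be computed for the effects of interest" and that P-"values and confidence intervals are considered descriptive".

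Section 2.8 says that "formal sample size calculation is not performed" and gives the target as follows: "We aim to include 100 pregnant females and their newborns/infants to obtain means and proportions with an acceptable range of uncertainty". With one-third loss to follow-up, 150 mothers are to be enrolled.

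Age appears as a predictor in one other place, section 2.9.2: "we will estimate the influence of main predictor variables, such as age, on the occurrence of missing data". The form in which age enters there is not stated.

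**The concern.** A variable measured on a fine scale is reduced to two extreme groups, and the women between them are left out of the comparison. Three things follow for this analysis.

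- **Precision.** With 100 evaluable pairs the contrast is about 25 against 25. The article rests its sample size on acceptable uncertainty for means and proportions, so an avoidable widening of intervals sits poorly with that rationale.
- **Transferability.** The quartile boundaries are set by whoever happens to enrol. A difference between sample-defined extremes is hard to compare with another cohort, whereas a slope per 5 years is not tied to these boundaries. The Discussion says that the study should generate hypotheses for larger confirmatory studies.
- **Shape.** If women of middle age differ from both ends, a contrast of the ends cannot show it.

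The stated aim includes finding demographic characteristics associated with skin microbiome development, so an age analysis does serve the study's purpose.

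**Working it through.** **The plan's own figure.** 100 / (1 − 1/3) = 150, which matches the enrolment number in section 2.8. The article states no precision or power for the age comparison, so there is nothing further to reproduce.

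**Inputs from the article.** 100 evaluable pairs and 150 enrolled (section 2.8); age metric, in years, 18 to 45 (Table 2); 95% confidence intervals (section 2.9).

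**Assumptions, not in the article.** A linear age effect; ages either normal (for the simulation, mean 32 and SD 5, limited to 18–45) or uniform over 18–45; age–outcome correlations of 0.2 to 0.4; a two-sided 5% test, used for illustration only.

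**Women used.** At n = 100, 25 + 25 = 50 against 100. At n = 150 (for example baseline outcomes), about 37 + 37 = 74 against 150.

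**Relative efficiency.** Let g be the gap in mean age between the two extreme quartiles, in SDs of age, and take the residual variance as 1.

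- Slope variance from the extreme quartiles at n = 100: (1/25 + 1/25) / g² = 0.08 / g².
- Slope variance from linear regression on all women: 1/100 = 0.01.
- Relative efficiency = 0.01 / (0.08 / g²) = g² / 8.

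| Age distribution | g | g²/8 | Variance ratio | Standard error ratio |
|---|---|---|---|---|
| Normal | 2 × φ(0.674)/0.25 = 2.542 | 0.81 | 1/0.808 = 1.24 | 1.11 |
| Uniform | 0.75 × √12 = 2.598 | 0.84 | 1/0.844 = 1.19 | 1.09 |

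The loss is equivalent to 100 × (1 − 0.844) ≈ 16 to 100 × (1 − 0.808) ≈ 19 of 100 women.

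**Width of the planned contrast.** The 95% half-width for the difference in means is 1.96 × √(2/25) = 0.55 outcome SDs at 25 per group, and 1.96 × √(2/37) = 0.46 at 37 per group.

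**Simulation (3,000 runs per setting, n = 100), continuous age against extreme quartiles.**

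| Correlation | Normal ages | Uniform ages |
|---|---|---|
| 0.2 | 0.53 vs 0.42 | 0.52 vs 0.45 |
| 0.3 | 0.87 vs 0.78 | 0.89 vs 0.80 |
| 0.4 | 0.99 vs 0.97 | 0.99 vs 0.98 |

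The simulated variance ratios at n = 100 (0.78 to 0.85) agree with the formula. The power loss is about 7 to 11 points at correlations of 0.2 and 0.3, and about 2 points or less at 0.4.

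**The case against.** Several counter-arguments carry weight.

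- **Scope.** A reader might infer that the plan throws away half of the cohort. It does not. The descriptive statistics, mother–infant correlations, mixed models and paired tests in section 2.9 are not limited to the extreme quartiles, and that section says that all available cases will be used. Within the age comparison, half of the women are left out but only about a sixth to a fifth of the information, because the extremes carry most of what there is on a linear trend.
- **Adjustment.** A reader might also infer that age can no longer serve as an adjustment variable. The article does not say so. Section 2.9.1 describes subgroup analyses, and nothing there bars continuous age from other models. That reading rests on silence.
- **Validity.** The contrast is inefficient but not biased. All results are declared descriptive, so power at 5% is not a criterion that this study sets itself. The sample size rationale concerns means and proportions, and age is called a main predictor only in connection with missing data.
- **Level of detail.** The form of covariates is commonly left to a full protocol or an analysis plan, neither of which is shown. This would answer a complaint about something missing. It does not answer this point, because the article states the form of the age comparison.
- **Assumptions.** The figures need linearity and an assumed age distribution. With a U-shaped relation, a single linear term could miss the effect just as the quartile contrast could. This is why the remedy needs a curvature check.
- **Endpoints.** Putting age only into the mixed models would leave ordinal or skewed endpoints without an age analysis beyond description. The remedy must cover them.

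What remains is that a stated analysis has a better alternative using data already collected, and the article gives no reason for leaving out the middle quartiles.

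**Conclusion.** The point holds as a minor, inexpensive improvement. The planned age comparison leaves out the middle half of the women and, under a roughly linear effect with normal or uniform ages, keeps about 81% to 84% of the information available from continuous age. It also ties the result to sample-dependent boundaries and cannot show the shape of the relation. These last two drawbacks do not depend on the assumed distribution or correlation. The size of the precision loss does, and the whole-year recording of age would make the quartiles only approximately a quarter each. The matter is efficiency and interpretability in one exploratory comparison. The documents do not support a claim of bias, of lost data elsewhere, or of age being unavailable for adjustment.

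**What to change.** In section 2.9.1, make continuous maternal age on all available women the main age analysis:

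- **Metric outcomes:** enter age in the linear mixed models already planned, with an age-by-time term and a simple curvature check such as a quadratic term. Report effects per 5 years with 95% confidence intervals.
- **Ordinal or skewed endpoints:** report Kendall's Tau between age and the outcome at each time point. Section 2.9 already plans this coefficient for the mother–infant associations.
- **Quartile comparison:** keep it as a descriptive display and report the quartile boundaries.

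The cost is a few more model parameters at about 100 pairs and a little more analysis work across the outcomes. No new data and no added burden on participants are needed.
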